### Intervention

In the experimental classroom, newly developed sit-to-stand desks replaced the regular desks. These sit-to-stand desks are called Adjust-Table Basic, and are manufactured and provided by Presikhaaf Schoolmeubelen, Arnhem, The Netherlands (https://www.schoolmeubelen.com). The desks have been designed to be easy to operate by young children. They are operated by a lever, which releases a gas spring lock. The gas spring allows very low-effort raising and lowering of the desktop. The desktops of the sit-to-stand desks have the same dimensions as the desktops of the regular desks (i.e., 500 × 700 × 18 mm). Height can be infinitely adjusted between 75 and 120 cm.

Each student in the experimental group received such a sit-to-stand desk, also the students that do not participate in the study. They will keep their sit-to-stand desks until they go to secondary school. The teacher of the experimental group also received a sit-to-stand desk (for adults). The students in the experimental group are not obligated to stand; rather, they are invited to stand, first by the mere opportunity to stand offered by the sit-to-stand desks (cf. affordance: the qualities or properties of an object that define its possible uses or make clear how it can or should be used), and second by the teacher who functions as a role model. For instructions, however, the teacher can order all children to sit for a proper view the (digital) blackboard at the front of the classroom. The students in the control group use their regular desks, as does their teacher.

### Primary outcome variables

Primary outcome measures are academic performance and the proportion of sitting time at school. Academic performance is assessed with the standardized and norm-referenced CITO test battery [43]. The standard procedure for most schools in The Netherlands is to assess academic performance twice each year with the CITO test battery. The scores of arithmetic, orthography, and reading comprehension are used in this study. Academic performance is assessed shortly before the week that sitting time is measured.

Sitting time is measured with an Activ8® Professional activity tracker [44, 45]. The Activ8® Professional (30 × 32 × 10 mm) is a 3D accelerometer that classifies postures and activities when worn on the upper leg: lying, sitting, standing, walking, cycling, and running. As with most other activity trackers, the Activ8® Professional is not able to validly identify all categories [28]. In youths, it can validly distinguish basic postures and activities (i.e., good to excellent validity), but has difficulty in distinguishing standing from other movements in complex activities; in complex activities, standing is often underestimated and detected as walking [44]. Each assessment (i.e., twice each year), an activity tracker is fixed on the upper leg of all participating students with a skin-friendly, waterproof, and transparent dressing (Tegaderm™, 3 M), halfway between the hip and knee. The activity tracker is worn for a school week during each assessment period: 24 h each day for five consecutive days from Monday morning till Friday afternoon. The recording interval is set at 10 s. At the end of the week data are collected via the Activ8® Professional recording tool.

### Secondary outcome variables

At each assessment period additional outcomes are measured following the week after sitting time is measured. Secondary outcomes are proportion of time spent in other postures and activities than sitting at school; proportion of sitting time and proportion of time spent in other postures and activities while awake outside school hours; cognitive skills; indicators of health; and indicators of wellbeing. Secondary outcome data, which may be influenced by the use of sit-to-stand desks [4, 19, 46–51], will be analyzed in relation to (changes in) sitting time.

The proportion of time spent in postures (i.e., lying, standing) and activities (i.e., walking, cycling and running) other than sitting at school are extracted from the Activ8® recordings. Additionally, to compare the proportion of time spent in postures and activities at school and outside school hours, the proportion of time spent in the different postures and activities outside school hours are also extracted. The times used for this are between 7:00 AM and 8:45 AM (the beginning of the school day), and between 3:00 PM (the end of the school day; 12:30 PM on Wednesdays) and 10:00 PM. Furthermore, the Activ8® recordings will also be used to compare posture and behavior with the wake up and sleep times recorded in the sleep diary.

Computer tests are used to study four dimensions of executive functioning that are related to and may underlie academic achievements: (I) working memory, (II) planning, (III) inhibition, and (IV) cognitive flexibility [52, 53]. All tests are presented using Inquisit 4 Computer Software [54] on a 15.6 in. ASUS N551 J 64-bit laptop computer screen. Completion of the four tests together takes between 30 to 60 min, dependent on the performance on each task. Children are administered the tests individually in a separate room under supervision of an assessor.

Handling working memory load is tested with the N-Back task [55, 56]. The N-Back task is a widely used working memory task that has face validity [57], although other types of validity, such as concurrent and convergent validity, are debatable [57–59]. In this modified version students are presented with a sequence of pictures (e.g., monkey, scissors, umbrella, chicken, cupcake), instead of letters. Pictures have been used in N-Back tasks before when testing with children [60, 61]. The task consists of indicating when the current picture matches the one from n steps before in the sequence. The load factor n is adjusted to make the task more or less difficult. In this study we use three levels: *n* = 1, *n* = 2, and *n* = 3. The first measure we use is the number of correct responses for each level. A high number of correct responses reflects a good handling of working memory load. The second measure is the mean response time for each level, which indicates the level of control over working memory processes [61, 62].

Planning is measured with the Tower of London task [63, 64]. This test starts with two pictures on the screen. Both pictures show a board with three vertical pegs of varying length, and three colored beads (i.e., red, blue and green). The first peg can hold three beads, the second two beads, and the third one bead. One picture shows the goal state and the other is the workspace board, where participants can rearrange the beads in the least number of moves from the start constellation to the goal state. There are twelve trials with increasing difficulty to complete. The first measure that is used is the total number of excess moves a participant makes beyond the minimum required moves. A low number of excess moves reflects good planning. The second measure of interest is the mean solution time. A low solution time reflects good efficiency on the task.

Inhibition is measured with an Inquisit version of the Fish Flanker test (FFT) [65]. The FFT is a basic derivative of the flanker visual filtering test that was developed by Eriksen and Eriksen [66]. The FFT is widely used to test one specific kind of response inhibition: the resistance to distractor interference. This refers to the ability to efficiently ignore irrelevant visual distractor information while processing target stimuli. A trial consists of a picture with five identical fishes. One fish in the center and two fishes on each side of the center fish. The direction the center fish is facing (i.e., direction of the head of the fish) determines what button should be pressed, left or right. All neighboring fishes move in the same direction as the center fish in congruent trials, or in the opposite direction in incongruent trials. Trials are interpreted as false in three cases: (I) when the wrong button is pressed; (II) when the response time to a trial exceeds 3000 milliseconds (an inattentive error); or (III) when the response time is shorter than 200 milliseconds (early response). The measures of interest are the number of erroneous responses and the mean response time, each registered for both the congruent and the incongruent trials. Both a low error rate and a low response time reflect good resistance to distractor interference.

Cognitive flexibility is measured with a digital version of the Wisconsin Card Sorting Task [67]. In this task a student is presented with cards that vary in the presented shapes on them, the color of the shapes, and the number of shapes. The student is to match the upper “example” card on the screen with one of four cards presented below the example card by clicking with the computer mouse on one of them. The sorting rule in effect is the dimension to which the correct choice matches the example card, and the student should find out what sorting rule is in effect. By using the feedback given to the student when making a correct or a false choice the student can theoretically find the sorting rule in effect after two trials. There are three categories, each containing four different values: (I) color, (II) form, and (III) number. Each category is presented twice. In our modified version, the criterion for successful completion of a category is applying the correct sorting rule four times in succession. After a streak of four correct responses, the sorting rule changes without the student being informed that it will. The maximum number of trials is set at 128. The measure of interest is the number of perseverative errors. This is the number of errors where the student continues to sort cards according to the same rule despite negative feedback. A low number of perseverative errors reflects good cognitive flexibility.

Indicators of health are measured with a number of tests and diaries. The 20-m Shuttle Run Test (SRT) is used to measure physical fitness [68]. The SRT is a widely used, and validated test [69]. It is a simple, easy to administer test, and a large number of individuals can be tested simultaneously. The SRT test consists of stages of continuous, incremental speed running between two lines 20 m apart. The initial speed is set at 8.5 km/h and increases by 0.5 km/h per minute. Audio signals indicate the speed. The test ends when a student fails to reach the end lines concurrent with the audio signals on two consecutive occasions. The reached stage is recorded. The assessment is carried out by an assessors together with the physical exercise teacher.

Hand dynamometry is used to measure grip strength. A hand dynamometer is a valid and reliable tool for measuring upper body strength and hand function [70]. Each student is tested with a calibrated Jamar® hydraulic dynamometer (J.A. Preston Corporation, Clifton, NJ). The dynamometer is set at the second handle position, and the standardized testing position for measuring grip strength is used [71]. The students are allowed a total of four attempts; twice with each hand. The highest score (in kg) for each hand is recorded by the assessor.

Lower body power is assessed by the assessor with the vertical jump, as first described by Sargent in 1921 [72]. The vertical jump is a practical, low-cost, reliable [73], and valid [74] test for two-legged explosive power. First the standing reach height is measured: the student stands straight beside a wall and reaches up with the hand closest to the wall, while keeping the feet flat on the ground. The point of the fingertips is recorded using a wall mounted measuring tape (Seca 206; Seca gmbh & co. kg., Hamburg, Germany). Then the student jumps vertically from a flat footed position and tries to touch the wall as high as she or he can. The highest point of three attempts is recorded. The distance to the nearest 0.5 cm between the standing reach height and the highest vertical jump height is the recorded score.

Each student’s weight (kg) and height (cm) is measured with light clothes and without shoes by the assessor. Weight is measured to the nearest 0.1 kg with a validated digital scale (Omron BF511; Omron Corp, Kyoto, Japan) [54]. Height is measured to the nearest 0.5 cm using a wall mounted measuring tape (Seca 206; Seca gmbh & co. kg., Hamburg, Germany). When measuring height, the student stands on a level floor with heels together; weight evenly distributed; heels, buttocks and shoulders against the wall; and arms loosely hanging at the sides with palms facing the thighs. BMI is calculated using the following formula: body mass/height^2^ (kg/m^2^). The scale used to measure body weight also allows bioelectrical impedance analysis of the body composition [75]. The student stands barefoot on metal footpads and grasps a handle with arms extended in front of her/his chest. Percentages of total body fat and total body muscle are measured with eight electrodes (two under each foot and two in each hand) and recorded.

A diary including the Dutch version of the Bristol Stool Form Scale for children (BSFSC) is used to report stool [76]. The BSFSC is a valid and reliable method for children to keep record of their stool [77]. At the start of the same week that the students wear their activity tracker, they receive their BSFSC. For five consecutive school days students write down their stool form (five categories ranging from “separate hard lumps like nuts” to “watery, no solid pieces), stool frequency, occasions of abdominal pain and pain during defecation, and whether they use medication for their stool.

In the same week that students keep a stool diary, they also keep a sleep diary. The diary is based on the Consensus Sleep Diary [78], which has become the de-facto sleep diary in sleep research, but has not yet been validated for children. With the sleep diary students keep track of the time they go to bed, fall asleep at night, get out of bed in the morning, and how often they wake up at night. They also rate their sleep and how well-rested they are, and report whether medication is needed to sleep. This diary is also used to confirm two transitions between inactivity and activity (i.e., the times of falling asleep and waking up) as recorded with the activity tracker. Parents are asked to remind the students to fill in both diaries.

Indicators of wellbeing are measured with questionnaires, which are assessed in the classroom under supervision of the teacher. A faces scale is used to measure happiness [79, 80]. The student answers to questions by indicating one face of a five-points-smiley-face-scale ranging from a green, happy face to a red, sad face. All six questions address the student’s feeling of happiness in general or in a specific situation (e.g., “How do you feel at the moment?” and “How do you usually feel at school?”). This questionnaire is not validated.

The KIDSCREEN-52 is a questionnaire to measure quality of life (QoL) in children and adolescents [81]. This is a reliable and valid, generic instrument that is used throughout many countries in the world [82]. The KIDSCREEN questionnaire consists of 52 items to be answered by the student. Students’ QoL is assessed in ten dimensions: physical well-being; psychological well-being; moods and emotions; self-perception; autonomy; relations with parents and home life; social support and peers; school environment; social acceptance (bullying); and financial resources. The items are five-point Likert scales to assess either the frequency (never to always) of certain behaviors/feelings or the intensity of an attitude (not at all to extremely). The recall period for each item is 1 week.

Satisfaction with the school environment is assessed with a short questionnaire. Eight items address the students’ satisfaction with the school building, their classroom, and their school furniture (e.g., “I am satisfied with how our classroom looks.” and “The furniture in our classroom is looking good.”). Students rate to what extent they agree or disagree on a four-point Likert-scale. These eight items are selected from the Dutch Quality Indicator in Primary Education (Kwaliteitsmeter Primair Onderwijs; Van Beekveld & Terpstra, Hoorn, The Netherlands); a commonly used, however non-validated, student questionnaire to rate the quality of a school.

Records of adherence and adverse events are also kept. Adherence is defined as the percentage of students in the experimental group who keep participating in the study measured at every test week. Adverse events are defined as any undesirable experience occurring to a subject during the study, whether or not considered related to the investigational product, testing procedures or experimental intervention. All adverse events reported spontaneously by the student or observed by a teacher, parent or assessor are recorded.

A complete list of primary and secondary outcome measures and supervision is provided as Additional file 2. Regarding supervision, assessors are present during computer testing, SRT, hand dynamometry, vertical jump, and height, weight, and body composition assessments. Teachers are present when students fill out questionnaires, and parents help the students to keep record of diaries.

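### The out-of-school posture outcome is named as waking time, but its fixed clock window to 10:00 PM does not exclude sleep

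*Protocol article*

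**What the plan says.** In the Protocol article, Secondary outcome variables, the outcome is named as "proportion of sitting time and proportion of time spent in other postures and activities while awake outside school hours". The same section then fixes the extraction times. For the morning: "The times used for this are between 7:00 AM and 8:45 AM (the beginning of the school day". For the rest of the day: "between 3:00 PM (the end of the school day; 12:30 PM on Wednesdays) and 10:00 PM". No other definition of the out-of-school period is given.

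The section also describes a sleep diary kept in the week the tracker is worn, in which "students keep track of the time they go to bed, fall asleep at night, get out of bed in the morning". Two uses of the diary alongside the tracker are stated. One is a comparison: "the Activ8® recordings will also be used to compare posture and behavior with the wake up and sleep times recorded in the sleep diary". The other is a check: "This diary is also used to confirm two transitions between inactivity and activity (i.e., the times of falling asleep and waking up". Neither sets the limits of the out-of-school window.

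Under Primary outcome variables, the tracker is worn "24 h each day for five consecutive days from Monday morning till Friday afternoon". It sorts time into lying, sitting, standing, walking, cycling and running. No sleep category is listed.

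**The concern.** The name of the outcome restricts it to waking time, but the extraction rule restricts it only by the clock. The children were 8 to 9 years old at recruitment, so some may well be asleep before 10:00 PM, and some after 7:00 AM. For those children, sleep enters the denominator of every out-of-school proportion and is assigned to one of the tracker's posture categories.

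Three uses of the data are exposed:

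- **School versus outside school.** This comparison is the section's stated reason for extracting the out-of-school data. School hours contain no night sleep, so only one side is diluted.
- **Change over time.** Assessments run from May 2017 to July 2019 and alternate between summer and winter. If bedtimes shift with age or season, the proportions shift too, even when waking behaviour does not.
- **Comparison of the groups.** This is exposed to a lesser degree, as shown below.

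**Working it through.** The plan gives no figure of its own to reproduce, so the check is clock arithmetic.

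**From the article.** The morning window is 7:00 to 8:45, or 1.75 h. The later window is 15:00 to 22:00, or 7 h; on Wednesday it is 12:30 to 22:00, or 9.5 h.

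- Ordinary day: 1.75 + 7 = 8.75 h.
- Wednesday: 1.75 + 9.5 = 11.25 h.
- Recordable week, taking wear to cover Monday to Thursday evenings and Tuesday to Friday mornings: 3 × 7 + 9.5 + 4 × 1.75 = 37.5 h.

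**Assumed, because the article gives no values.** Sleep onset is varied from 20:00 to 22:00, with waking by 7:00. The true waking sitting share is set at 60% for illustration.

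**Formulas.** Share asleep s = (22:00 − onset) / window length; for the week, s = 4 × (22:00 − onset) / 37.5. If sleep is recorded as lying, reported sitting = 0.60 × (1 − s).

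| Assumed onset | s, ordinary day | s, Wednesday | s, week | Reported sitting, ordinary day | Reported sitting, week |
|---|---|---|---|---|---|
| 20:00 | 22.9% | 17.8% | 21.3% | 46.3% | 47.2% |
| 20:30 | 17.1% | 13.3% | 16.0% | 49.7% | 50.4% |
| 21:00 | 11.4% | 8.9% | 10.7% | 53.1% | 53.6% |
| 21:30 | 5.7% | 4.4% | 5.3% | 56.6% | 56.8% |
| 22:00 | 0% | 0% | 0% | 60.0% | 60.0% |

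For example, at 20:30 on an ordinary day, s = 1.5 / 8.75 = 0.171 and 0.60 × 0.829 = 0.497.

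**Direction.** If the tracker reads sleep as sitting instead, reported sitting = 0.60 × (1 − s) + s. At 20:30 that is 0.497 + 0.171 = 0.669, so sitting is overstated.

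**Time trend.** With sleep recorded as lying, a shift in onset from 20:30 to 21:00 moves reported sitting by 53.1 − 49.7 = 3.4 points on an ordinary day and 53.6 − 50.4 = 3.2 points over the week, with no change in behaviour.

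**Group contrast.** If s is equal in both groups, a true difference d is reported as d × (1 − s). At 20:30 on an ordinary day that is 0.829d, which is attenuation. A spurious difference needs sleep to differ by group: a 30-minute difference gives 0.60 × (0.5 / 8.75) = 3.4 points.

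**The case against.** The strongest reply is that the size rests wholly on assumed bedtimes. That stands: at 22:00 the effect is nil, and the children grow older during follow-up, so later onsets become more relevant. A reader might infer that the plan demonstrably counts sleep as waking time for all children. The article supports only that nothing prevents it.

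A fixed window is also reproducible and identical in both groups, whereas sleep is itself a measured outcome that the desks might affect. A denominator bounded by sleep would then depend on something measured after allocation. This is a fair trade-off, and it is why the fixed window should be kept as a sensitivity analysis. It does not make the fixed window a measure of waking time.

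It can be said that the diary and tracker are already linked, and that trimming rules belong in a fuller document. But the article does state a rule, with clock times, and the diary's stated roles are comparison and confirmation.

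Several stronger readings are not supported:

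- The diary does not give the true times. It is child-reported and, by the article's own account, not validated for children.
- The direction of bias is not settled. The article does not say how the tracker classifies sleep, and it concedes that the device cannot validly identify every category.
- Testing whether children compensate at home for sitting less at school is not a stated purpose.
- The Monday-to-Friday wear period is no defect. It is openly stated, and nothing says that unworn hours enter a proportion.

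**Conclusion.** The concern holds as a mismatch between a secondary outcome's name and the rule that computes it. On an ordinary day, each half hour of sleep before 10:00 PM puts 0.5 / 8.75 = 5.7% of non-waking time into the denominator (0.5 / 11.25 = 4.4% on Wednesday). Over the recordable week, sleep would fill about 16.0% of the window at an assumed onset of 20:30 and 10.7% at 21:00. Sleep after 7:00 AM would add to this, and waking time before 7:00 AM or after 10:00 PM is left out.

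If sleep is recorded as lying, sitting is understated and lying overstated; if it is read as sitting, the error in sitting reverses. Either way, the comparison with school hours is distorted and changing bedtimes can produce a trend.

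A reader might infer that the trial's group comparison is biased. The article does not support that: with similar sleep in the two groups the contrast is mainly attenuated, and any shared trend appears in the control group as well. Both primary outcomes, academic performance and sitting time at school, are untouched. The matter is worth correcting because the correction is cheap, but it does not threaten the main conclusions.

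**What to change.** As the main definition, bound each child-day's out-of-school window by the diary's wake and fall-asleep times, checked against the tracker's transitions between inactivity and activity, a match the article already foresees. Use the fixed window where a diary entry is missing, and report it for all children as a sensitivity analysis. If the fixed window is kept as the main definition, stop describing the measure as waking time and state that it may include sleep.

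The change needs no new data, only a different cut of recordings and diaries already collected. The downside is that diary times are child-reported, not validated for children and sometimes missing, and that the denominator then varies with each child's sleep. The sensitivity analysis shows how much this matters.

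### Flanker task: low raw times and errors on both trial types are read as resistance to interference, so a between-class change in general speed would be labelled an inhibition effect

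*Protocol article*

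**What the plan says.** The Protocol article, Methods, Secondary outcome variables, gives the target of the task: "The FFT is widely used to test one specific kind of response inhibition: the resistance to distractor interference". It explains the term: "This refers to the ability to efficiently ignore irrelevant visual distractor information while processing target stimuli". The two trial types are described so: "All neighboring fishes move in the same direction as the center fish in congruent trials, or in the opposite direction in incongruent trials".

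Scoring follows. "The measures of interest are the number of erroneous responses and the mean response time", "each registered for both the congruent and the incongruent trials". That makes four measures: errors and time, each for two trial types. A trial counts as false for a wrong button, for a response slower than 3000 ms (which the article itself calls inattentive) or for one faster than 200 ms.

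The reading of the scores is then fixed in one sentence: "Both a low error rate and a low response time reflect good resistance to distractor interference".

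The same section says that secondary outcomes "will be analyzed in relation to (changes in) sitting time". The Statistical analysis section plans mixed growth models with age, gender and baseline outcomes as explanatory variables. It extends this to some secondary outcomes without naming them. Neither section names a difference, ratio or interaction between trial types.

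**The concern.** The reading does not match the construct that the article defines a few sentences before. A child who fails entirely to ignore congruent flankers still presses the right button, because the flankers agree with the target. A fast, accurate congruent score therefore shows speed and accuracy; it gives no evidence of resisting a conflicting distractor. An incongruent score does contain the interference cost, but added to everything else that makes a child fast or slow, attentive or not.

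What is at stake is the label on a result. The article treats inhibition as one of four separate dimensions of executive functioning. There is one class per arm, and children are followed for two and a half years from age 8–9. A difference between the classes in how general speed, alertness or ease with the computer develops cannot be separated from the desks, and under the stated reading it would be reported as an effect on inhibition. The same holds within children: if less sitting goes with quicker responding in general, the association would be reported as one with inhibition.

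**Working it through.** The plan states no figure to reproduce. The check is a decomposition of the scores, with assumed times because the article gives no flanker data.

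**Inputs from the article:** two trial types; raw mean time and error count for each; low values read as good resistance; no neutral (target-alone) trial described; 19 children per class, 38 in all.

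**Model.** Let g be a child's general response time, k the cost of opposing flankers and f the help from agreeing flankers.

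- Congruent mean: C = g − f
- Incongruent mean: I = g + k
- Contrast: I − C = k + f

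The general component g is in both raw means and cancels in the contrast. The contrast holds facilitation as well as interference.

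**Uniform gain in speed of s ms (assumed).** C becomes C − s, I becomes I − s, and the contrast is (I − s) − (C − s) = I − C.

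| s (ms) | change in C | change in I | change in I − C |
|---|---|---|---|
| 20 | −20 | −20 | 0 |
| 40 | −40 | −40 | 0 |
| 50 | −50 | −50 | 0 |
| 100 | −100 | −100 | 0 |

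The stated reading reports better resistance in every row; the contrast reports no change.

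**Ranking of two children (assumed times).**

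- Child A: C = 600, I = 680, contrast 680 − 600 = 80 ms.
- Child B: C = 800, I = 840, contrast 840 − 800 = 40 ms.

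A is better on both raw times, B on the contrast. The values were chosen to show that a reversal is possible; they say nothing about how often it occurs.

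**Which differences between classes matter.** A stable difference d in general speed is present at baseline and at follow-up, so adjustment for baseline largely removes it. Growth common to both classes cancels in the comparison of arms. What remains is a change that differs between classes: an extra gain of s in one class gives an arm difference of −s in both C and I and 0 in the contrast. A true fall of t in interference cost gives 0 in C, −t in I and −t in the contrast. The two cases are therefore distinguishable, but only by comparing trial types.

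**Limit of the additive model.** If times shrink by a common factor r, the contrast shrinks too, from I − C to r(I − C). For child A its shift is 80/680 = 12% of the shift in the raw incongruent time. The contrast is then much less affected, but not immune.

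**Errors.** Lapses over 3000 ms and anticipations under 200 ms enter the count on both trial types. Those equally likely on both cancel in a contrast of error proportions; in the raw count they are read as failed inhibition.

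**The case against.** The quoted sentence can be taken as a note on direction of scoring. The other executive-function tasks close with similar sentences, and none of them prescribes how the arms are compared. Times and errors are kept apart by trial type and nothing says that they will be pooled, so a contrast can be formed later, and a derived variable for one secondary task is the kind of detail that an analysis plan may hold. This stands as far as it goes: a missing contrast alone would not be a finding. But the article also writes down what the measures mean, for all four of them, and that statement is unsound for the congruent pair.

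It can also be said that the article's definition speaks of irrelevant distractors in general, and that congruent trials show flankers too. That is so, but failing to ignore those flankers carries no penalty in the score, so a low value there cannot show that they were ignored.

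A reader might infer that the inhibition question goes unanswered, or that any response-time effect would be an artefact. The documents do not support that. Incongruent times and errors carry interference information. Separate registration lets a reader see whether an effect appears on both trial types or mainly on incongruent ones. Baseline adjustment, where it is applied, deals with stable differences in speed. Nor do the documents show that general speed will in fact change differently in the two classes; all millisecond values above are assumed.

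**Conclusion.** The point holds as a fault in a written interpretation rule. Two of the four listed measures (congruent time and congruent errors) do not measure resistance to conflicting distractors, and the other two measure it mixed with general speed and attention. The consequence is conditional: an arm comparison is mislabelled only if general speed or attention changes differently in the two classes, and the analysis against sitting time only if general speed tracks sitting time. With one class per arm the first cannot be excluded. Its size cannot be given from the documents; under a uniform shift it equals the shift itself. One secondary outcome is affected, the data needed are already collected, and the priority is low.

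**What to change.** Base the inhibition conclusion on the incongruent-versus-congruent contrast, for response time and for errors. The preferred form is an arm by trial-type interaction (by time) in the planned mixed model, with both trial types as repeated outcomes within child. For the analysis against sitting time, use the corresponding sitting-time by trial-type term. Use error proportions if the number of trials differs by type. Keep reporting the raw incongruent and congruent values alongside, and describe the congruent ones as general speed and accuracy only. Amend the interpretation sentence to match.

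No new data are needed. The costs are statistical: the contrast carries the measurement error of two means while the variation they share cancels, so it is less reliable than either part, which matters with 38 children. Without neutral trials it combines interference with facilitation, and the report should say so. A null interaction should therefore be shown with its confidence interval and not read as evidence of no effect on inhibition.
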